## 8.2 Causality Assessment

The Investigator and the Local Safety Monitor both determine causality. It is expected that communication and consultation may occur in the assessment of the causality of AEs. The greatest degree of causal relationship (definite > probable > possible > unlikely related > not related) determined by either the Investigator or Local Safety Monitor after their discussions (and review of the volunteer if necessary) will determine the ultimate classification of the AE. Definite (4), probable (3) and possible (2) are considered to be related. No relationship (0) and unlikely (1) are considered to be unrelated. The following guidelines will be used to assess the relationship of all AEs to the administration of the vaccine, with the premise that all local reactions will be considered causally related to the vaccination:

0 = No relationship:

- No temporal relationship to vaccine; and
- Alternate aetiology (clinical state, environmental or other interventions); and
- Does not follow known pattern of response to the vaccine

1 = Unlikely relationship:

- Unlikely temporal relationship to vaccine; and
- Alternate aetiology likely (clinical state, environmental or other interventions); and
- Does not follow known typical or plausible pattern of response to the vaccine

2 = Possible relationship:

- Reasonable temporal relationship to vaccine; or
- Event not readily produced by clinical state, environmental or other interventions; or
- Similar pattern of response to that seen with the vaccine

3 = Probable relationship:

- Reasonable temporal relationship to vaccine; and
- Event not readily produced by clinical state, environment, or other interventions or

- Known pattern of response seen with the vaccine
- 4 = Definite relationship:
- Reasonable temporal relationship to vaccine; and
  - Event not readily produced by clinical state, environment, or other interventions; and
  - Known pattern of response seen with the vaccine

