#### **\* Change to Group 2 vaccinations**

A change has been made for group 2 volunteers due to receive their day 28 boost vaccination on or after 2 September 2015, due to a higher frequency of mild respiratory adverse events in this group. Local (skin) and systemic symptoms were as expected and consistent with data from previous studies. These volunteers will not receive the day 28 boost vaccination, but instead will receive a placebo by both intradermal and aerosol inhaled routes to maintain blinding. Additional safety and immunological information will be gained by continuing with day 35 bronchoscopy in these volunteers. Any volunteer not wishing to proceed in this manner will remain in follow up with no vaccination or bronchoscopy.

As BCG is protective in childhood, it is routinely given at birth in TB endemic countries but is also in widespread use in children and adolescents in much of the rest of the world. Therefore, as in previous trials of intradermal MVA85A, we propose to vaccinate BCG-primed subjects. These will be healthy men and women aged 18-55 years who have been previously vaccinated with BCG.

All subjects will have received BCG vaccination at least six months prior to enrolment. MVA85A ( $5 \times 10^7$  pfu) or saline placebo will be administered by systemic (intradermal) or aerosol (Omron jet nebuliser) route (paired placebo design). The interval between the two vaccinations is one month.

In order to minimise the risk from bronchoscopy, subjects with a history or evidence of lung disease will be excluded. This will be determined by our standard screening procedures (history, examination, urine analysis, and blood tests), and, in addition, a chest x ray and pulmonary function testing.

The peak effector T-cell response in blood is ~7 days post-vaccination with MVA85A. Pulmonary mucosal responses are expected to follow a similar time course and a preclinical study has demonstrated this in non-human primates (35). Thus bronchoscopy and bronchialveolar lavage will be performed seven days after each vaccination.

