## 4.2 Randomisation

In order to reduce bias and the influence of any difference in the baseline characteristics between the three groups, we have chosen to randomise the allocation of subjects. This aims to achieve a balance between the three groups in any important confounding factors such as levels of pre-existing antimycobacterial immunity (influenced by, for example, country of origin and length of time elapsed since prior BCG vaccination). This will be performed by variable block randomisation using sequentially numbered sealed envelopes, prepared by an independent colleague at the Centre for Statistics in Medicine, to ensure allocation concealment. Volunteers are blinded as they will receive a paired placebo at the same time of vaccination. The bronchoscopist will be blinded to the route of vaccine administration. This is intended to eliminate any bias in the reporting of the appearance of the lung mucosa and extent of airway inflammation. In addition, the postdoctoral researcher in the laboratory overseeing the immunological analyses will also be blinded to reduce any bias that could be introduced at the sample processing stage. All samples will be anonymised.

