### **Trial regimen**

Group 1: Aerosol inhaled MVA85A  $5 \times 10^7$  pfu (and intradermal saline placebo) on day 0, followed by homologous boosting with MVA85A  $5 \times 10^7$  pfu intradermal on day 28 (and aerosol inhaled saline placebo)

Group 2: Intradermal MVA85A  $5 \times 10^7$  pfu (and aerosol inhaled saline placebo) on day 0, followed by homologous boosting with MVA85A  $5 \times 10^7$  pfu aerosol inhaled on day 28 (and intradermal saline placebo) OR, following safety amendment (see section 4.1)

Intradermal MVA85A  $5 \times 10^7$  pfu (and aerosol inhaled saline placebo) on day 0, followed by aerosol inhaled saline placebo and intradermal saline placebo on day 28

Group3: Intradermal MVA85A  $5 \times 10^7$  pfu (and aerosol inhaled saline placebo) on day 0, followed by homologous boosting with MVA85A  $5 \times 10^7$  pfu intradermal on day 28 (and aerosol inhaled saline placebo)

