## **6.2 Saline**

Sterile saline (0.9%) will be used for dilution and placebo doses. The volume of saline used as placebo will be identical to the vaccine volume by the same route. For volunteers receiving the aerosol vaccination we will administer  $5 \times 10^7$  pfu of vaccine made up to 1ml with saline and at the same time a paired placebo of 135 microlitres of normal saline for intradermal injection. For volunteers receiving the vaccine intradermally we will administer  $5 \times 10^7$  pfu of vaccine made up with normal saline to a vaccine volume of 135 microlitres and at the same time a paired placebo of 1ml of saline inhaled. We require 60ul of MVA85A vaccine to give a dose of  $5 \times 10^7$  pfu. For the aerosol vaccine the total volume is 1ml, i.e. ~940 microlitres of saline and 60 microlitres of vaccine. The volume for intradermal injection is 135 microlitres, i.e. ~75 microlitres of saline with 60microlitres of vaccine.

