## 8.3 Clinical Assessment

All AEs (whether reported by the subject or solicited by the Investigator) will be clinically assessed at each visit and recorded with start and stop dates and details of any treatment undergone. Final grading of adverse events will be determined by the Investigator on the trial.

This information will be **collected** as follows:

- Subjects are asked to complete diary cards for 14 days after MVA85A vaccination by either route. They are provided with a thermometer and tape measure to enable daily recording of temperature and local redness and swelling at the intradermal injection site. They are also provided with a spirometer to record pulmonary function.
- Outside the diary card periods, expected local and systemic AEs (listed in table 4 below) will be solicited, in other words specifically asked about at each visit, and graded by severity and causality (as detailed in sections 9.2 and 9.4).
- Subjects will be given the opportunity to report any other new symptoms since the last visit with start and stop dates and any treatments undergone.
- Vital signs will be performed in the normal manner at each visit.
- The overall appearance of the lung mucosa will be assessed at the day 7 bronchoscopy.

|                               | Adverse event                                 |
|-------------------------------|-----------------------------------------------|
| Local (intradermal route)     | Pain/tenderness at the injection site         |
|                               | Redness at the injection site                 |
|                               | Swelling at injection site                    |
|                               | Warmth at the injection site                  |
|                               | Itch at the injection site                    |
|                               | Scaling/pustules at the injection site        |
| Local (aerosol inhaled route) | Cough                                         |
|                               | Sore throat                                   |
|                               | Wheeze                                        |
|                               | Shortness of breath                           |
|                               | Sputum                                        |
|                               | Haemoptysis                                   |
|                               | Chest pain                                    |

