# **9. STATISTICS**

## **9.1 Statistics**

This is primarily a trial with descriptive endpoints. Twelve subjects will be recruited into each arm of the trial (i.e. 36 in total). Our previous experience with clinical trials using MVA85A over the last 10 years suggests that this sample size is a feasible number to recruit, screen, enroll, and follow up in practical terms, whilst also allowing the determination of any substantial and clinically significant differences in safety and cell-mediated immunity between the three groups. A twofold increase in the magnitude of the cellular immune response (as measured by Elispot response to 85A peptide stimulation) is considered immunologically meaningful. Extrapolating effect size and variability from the completed initial aerosol vaccine safety study (TB026), twelve volunteers are needed to have 80% power to detect an immunologically meaningful difference in the summed peptide pools and 8

volunteers to achieve the same for single peptide pool of 85A. This sample size is appropriate for a proof-of-concept Phase I safety study.

It is anticipated that the immunological endpoints will not follow a normal distribution. A log transformation will be applied and if the resulting data are normally distributed they will be summarised by group using means and standard deviations. The one-week and six-month responses will be compared between the three groups using a t-test. If the resulting data are not normally distributed then medians and interquartile ranges will be used to summarise the data and the Mann Whitney U test will be used for statistical comparisons. An area-under-curve analysis will be used to compare the overall responses over time between the three groups. This analysis will make use of data collected at all time points.

Differences between means or medians between the three groups will be presented along with their 95% confidence intervals. Within each group, paired data will be analysed using either a paired t-test or the Wilcoxon matched pairs test depending on the normality of the data.

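### Section 8.2 makes every local reaction vaccine-related although half of the planned administrations are saline, so for local reactions that label cannot separate MVA85A from saline

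*Protocol*

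**What the plan says.** Section 8.2 has the Investigator and the Local Safety Monitor "assess the relationship of all AEs to the administration of the vaccine". One condition is fixed in advance of any rating, and it reads: "with the premise that all local reactions will be considered causally related to the vaccination". The section makes no exception for saline. Grades 2 to 4 count as related, and the higher of the two raters' grades stands.

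The design pairs vaccine with saline. Section 4.2 states: "Volunteers are blinded as they will receive a paired placebo at the same time of vaccination". Section 6.2 gives aerosol vaccine recipients "at the same time a paired placebo of 135 microlitres of normal saline for intradermal injection", and gives intradermal vaccine recipients 1 ml of inhaled saline.

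Section 4.1 (Change to Group 2 vaccinations) says that Group 2 volunteers due their boost from 2 September 2015 go without it and "instead will receive a placebo by both intradermal and aerosol inhaled routes to maintain blinding". Section 6.1 (Trial regimen) agrees: intradermal MVA85A on day 0, "followed by aerosol inhaled saline placebo and intradermal saline placebo on day 28".

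Table 4 in Section 8.3 lists solicited local events for both routes and does not link them to the product given. On diaries, Section 8.3 says: "Subjects are asked to complete diary cards for 14 days after MVA85A vaccination by either route". Table 1 issues diary cards on days 0 and 28 and makes no exception for any group.

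**The concern.** The Section 8.2 premise suits a trial in which whatever is given by a route is vaccine. Here, redness at a saline injection or cough after inhaled saline is declared vaccine-related before the 0 to 4 criteria are consulted. The mismatch is plainest at the double-saline visits: the rule links a local reaction to a vaccination that Section 4.1 says is not given that day.

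The primary objective compares the safety of aerosol and intradermal MVA85A, and the Group 2 change was prompted by respiratory events. A summary of related local reactions would credit intradermal MVA85A with airway reactions to inhaled saline, and aerosol MVA85A with skin reactions to injected saline. Relatedness also has uses elsewhere in the protocol: Section 8.1 defines an adverse reaction by it, and Section 8.6 makes follow-up after the end of the trial depend on it.

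**Working it through.** **Inputs.** Section 9.1: 3 arms of 12, so 36 volunteers. Section 4.1: two vaccination visits. Sections 6.1 and 6.2: two administrations per visit, one by each route, as follows under the unamended regimen.

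| Group (n = 12 each) | Day 0 aerosol | Day 0 intradermal | Day 28 aerosol | Day 28 intradermal |
|---|---|---|---|---|
| 1 | MVA85A | saline | saline | MVA85A |
| 2 | saline | MVA85A | MVA85A | saline |
| 3 | saline | MVA85A | saline | MVA85A |

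**Count, unamended regimen.**
- All administrations: 36 × 2 × 2 = 144, with 72 by each route.
- Saline by aerosol: 12 (Group 1, day 28) + 12 (Group 2, day 0) + 24 (Group 3, both days) = 48; 48/72 = 66.7%.
- Saline intradermally: 12 (Group 1, day 0) + 12 (Group 2, day 28) = 24; 24/72 = 33.3%.
- Together: 72/144 = 50%.

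**Count, after the Group 2 change.** Let k volunteers proceed with double saline and d decline, with k + d at most 12. Neither number is in the protocol. Each volunteer who proceeds turns one MVA85A dose into saline. Each who declines removes one MVA85A and one saline administration. The saline share is (72 + k − d)/(144 − 2d).
- k = 0, d = 0: 72/144 = 50.0%.
- k = 12, d = 0 (ceiling): 84/144 = 58.3%; by aerosol, (48 + 12)/72 = 83.3%.
- k = 0, d = 12: 60/120 = 50.0%.

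For each volunteer who proceeds, both day 28 administrations are saline.

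**What the premise does.** It grades by type of event (local) and ignores what was given by that route. For local events, relatedness is thus constant across MVA85A and saline, and a constant label cannot discriminate. The aerosol route is the more exposed, since two thirds or more of its planned administrations are saline.

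**What limiting the premise would change.** *Possible* (grade 2) needs only one of three criteria: plausible timing after vaccine, no ready explanation in clinical state, environment or other interventions, or a pattern resembling known vaccine responses.
- At a paired visit, MVA85A is given by the other route at the same time. A reaction soon after saline meets the timing criterion and still grades at least 2, so the label mostly stays as it is.
- At a double-saline visit, the last MVA85A was the day 0 prime, about 28 days before. Timing no longer clearly supports relatedness, although the pattern criterion can still yield grade 2.

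Rewording Section 8.2 therefore removes a false statement, but does not by itself make the relatedness label usable for comparing routes.

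**Diaries.** Read literally, Section 8.3 asks for no diary after a double-saline visit, whereas Table 1 issues one on day 28 to everybody. Section 7.5 has procedures follow Table 1.

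**The case against.** The premise is cautious and uniform. Section 8.1 counts an event as an adverse reaction when a relationship cannot be excluded, and Section 4.2 does not list the causality raters among those blinded. A fixed rule stops a rater who may know the allocation from discounting some local reactions. This stands as a reason for caution in single cases, but does not make the label informative in a comparison with saline.

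No analysis stated in the protocol depends on relatedness, and tabulation is commonly left to the analysis plan. That stands too, and it limits the consequence. The point is only that a rule written in the protocol does not fit the protocol's own design.

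*Vaccination* might mean the whole paired procedure: the trial summary speaks of vaccination by both routes. But Section 4.1 contrasts the boost vaccination with placebo, and Section 8.2 refers to administration of the vaccine. The narrower reading is better supported.

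Three stronger readings are tempting, and the protocol does not support them.
- *The safety comparison is biased.* It is not. Events are recorded whatever their cause, Table 4 separates them by route, and the regimen fixes the product by group, route and visit.
- *The double-saline volunteers are the natural control for the respiratory signal.* They are defined by calendar date. Group 3 on day 28, with the same intradermal prime followed by inhaled saline and intradermal MVA85A, is the randomised comparator.
- *Double-saline volunteers would have no diary.* Table 1 and Section 7.5 largely settle that they would; the fault is loose wording in Section 8.3.

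**Conclusion.** The point holds, with a modest consequence. The stated premise misclassifies local reactions at saline routes, which are 72 of 144 planned administrations, and most clearly those at double-saline day 28 visits. For local reactions, relatedness cannot distinguish MVA85A from saline. Recording of events and the all-cause comparison between randomised arms are intact.

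The 50% share follows from the protocol alone. The share after the Group 2 change, 50.0% to 58.3%, depends on unstated numbers of volunteers.

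A reader might go on to infer a count of misclassified events. If saline caused a local reaction in 10% to 30% of administrations, the count would be 72 × 0.10 = 7.2 to 72 × 0.30 = 21.6. That rate is an assumption found nowhere in the protocol. Most such events at paired visits would also be graded at least *Possible* without the premise, so they cannot be charged to that sentence. No count should be reported.

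**What to change.** 1. In Section 8.2, state that the automatic premise applies only to the route that carried MVA85A at that visit. Assign this at analysis from the administration record, so that raters need not be told the allocation.
2. Do not use relatedness to compare routes for local reactions. Tabulate them irrespective of causality in four columns: MVA85A aerosol, MVA85A intradermal, saline aerosol, saline intradermal. Show double-saline day 28 visits separately, and name Group 3 on day 28 as the randomised comparator for respiratory events after the boost.
3. Reconcile the diary wording in Section 8.3 with Table 1, so that both describe the same administrations.

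The cost is two wording changes and one extra table. Local reactions would also need an ordinary 0 to 4 rating, because the raters would not know which of them the premise covers. The product by group, route and visit is already fixed by Section 6.1, so no new data are needed.

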## 8.3 Clinical Assessment

All AEs (whether reported by the subject or solicited by the Investigator) will be clinically assessed at each visit and recorded with start and stop dates and details of any treatment undergone. Final grading of adverse events will be determined by the Investigator on the trial.

This information will be **collected** as follows:

- Subjects are asked to complete diary cards for 14 days after MVA85A vaccination by either route. They are provided with a thermometer and tape measure to enable daily recording of temperature and local redness and swelling at the intradermal injection site. They are also provided with a spirometer to record pulmonary function.
- Outside the diary card periods, expected local and systemic AEs (listed in table 4 below) will be solicited, in other words specifically asked about at each visit, and graded by severity and causality (as detailed in sections 9.2 and 9.4).
- Subjects will be given the opportunity to report any other new symptoms since the last visit with start and stop dates and any treatments undergone.
- Vital signs will be performed in the normal manner at each visit.
- The overall appearance of the lung mucosa will be assessed at the day 7 bronchoscopy.

|                               | Adverse event                                 |
|-------------------------------|-----------------------------------------------|
| Local (intradermal route)     | Pain/tenderness at the injection site         |
|                               | Redness at the injection site                 |
|                               | Swelling at injection site                    |
|                               | Warmth at the injection site                  |
|                               | Itch at the injection site                    |
|                               | Scaling/pustules at the injection site        |
| Local (aerosol inhaled route) | Cough                                         |
|                               | Sore throat                                   |
|                               | Wheeze                                        |
|                               | Shortness of breath                           |
|                               | Sputum                                        |
|                               | Haemoptysis                                   |
|                               | Chest pain                                    |
| Systemic                      | Documented fever (oral temperature > 37.5° C) |
|                               | Symptoms of feverishness                      |
|                               | Malaise                                       |
|                               | Arthralgia                                    |
|                               | Headache                                      |
|                               | Myalgia                                       |
|                               | Nausea / vomiting                             |

Table 4: Routinely solicited local and systemic adverse events

The information will be **recorded** as follows:

- During the diary card period, all solicited AEs (listed in table 4) and any additional unexpected AEs are captured in the diary card and at clinic visits (CRF)
- Outside the diary card periods all AEs will be documented in the AE line listing section of the CRF with start and stop dates and details of any treatments undergone.
- Vital signs will be recorded in the CRF.

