### *Safety profile*

The typical local reaction as a result of intradermal injection of MVA85A is temporary pain, redness and swelling at the site of the injection with a 5-10 mm central red swollen area and a paler red area ranging from 5-10 mm in diameter which peaks at 48 hours post vaccination. At seven days post vaccination, only the central area of redness remains. This fades over a few weeks and is not usually apparent eight weeks after vaccination. No signs of any Koch type reaction in subjects infected with *M. tb*, has been seen with this or any other candidate vaccine to date.

Systemic reactions to the vaccine are short-lived, and resemble influenza symptoms including fatigue, headache, malaise, feverishness, and muscle aches. These systemic symptoms are typically mild and occur in 50-90% of all subjects.

The preliminary analysis of local and systemic reactions induced by the aerosol route that were reported in the completed Phase I safety study are summarised in section 4.4 "Risks and Benefits".

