##### *Local reaction from aerosol inhaled vaccination*

Enrolment for the first ever trial administering a virally vectored vaccine by the aerosol route has just been completed in our group. The trial was single blinded paired placebo, so all volunteers received either an intradermal vaccine with saline by aerosol or vice versa. There was no significant difference between systemic adverse events, respiratory adverse events or pulmonary function tests between the two groups.

Constitutional influenza-like symptoms such as fatigue, headache, malaise, feverishness, and muscle aches can occur with any vaccination lasting for 2-3 days. In the case of MVA85A, fatigue and headache are most common, occurring in 50-90% of subjects, and these are nearly always mild. Presyncopal and syncopal episodes may occur at the time of vaccination which rapidly resolve. As with any other vaccine, temporary ascending paralysis (the Guillain-Barré syndrome, GBS) or immune mediated reactions that can lead to organ damage may occur. For influenza vaccines an excess of approximately 1 GBS case per million persons immunized has been observed. No cases were observed in people under 45 years of age. However, this has never been seen with the MVA85A vaccine or vaccines containing any of its components.

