## **4.5 Data Collection**

The bronchoscopic procedure is not being assessed for safety as it is a standard medical technique with a known profile of expected risks as described in section 4.4. Vaccination safety data for both routes will be collected both actively and passively as follows:

- Information about local and systemic adverse events will be collected at each visit by medical history, examination and measurement of the injection site, pulmonary function testing, bronchoscopic examination of the lungs, and the use of diary cards.
- Vital signs will be recorded at each visit.
- Safety blood tests (FBC, LFT, U&E) will be collected at screening and day 7.

This information will be entered into the CRF contemporaneously at each visit. Results of laboratory investigations and immunological data will be entered into the CRF. The CRFs will be the source data for this trial.

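### Table 4 omits fatigue, which the protocol names among the two most common MVA85A reactions, and the day 7 wording in Sections 4.5 and 8.3 contradicts Table 1

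*Protocol*

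**What the plan says.** **Expected reactions.** In Section 2.1 the safety profile says systemic reactions "resemble influenza symptoms including fatigue, headache, malaise, feverishness, and muscle aches". Section 4.4 repeats that list and adds: "In the case of MVA85A, fatigue and headache are most common, occurring in 50-90% of subjects, and these are nearly always mild". Both places name fatigue and malaise as separate symptoms.

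**What is asked about.** Section 8.3 presents Table 4 as the expected events about which volunteers are specifically questioned. Its systemic rows are documented fever, feverishness, malaise, arthralgia, headache, myalgia and nausea/vomiting. There is no fatigue row. For the 14-day diary period the rule is "During the diary card period, all solicited AEs (listed in table 4) and any additional unexpected AEs are captured in the diary card"; visits to the clinic are a second source. Section 8.3 also opens by requiring that all adverse events be assessed and recorded, whether solicited or reported by the volunteer, and it lets volunteers mention any other new symptom.

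**When bloods and mucosa are assessed.** Section 4.5: "Safety blood tests (FBC, LFT, U&E) will be collected at screening and day 7". Section 8.3: "The overall appearance of the lung mucosa will be assessed at the day 7 bronchoscopy". Table 1, however, marks biochemistry at screening and days 2, 7, 30 and 35, haematology at screening and days 7 and 35, and bronchoscopy on days 7 and 35. Table 3 and Section 4.1 put a bronchoscopy one week after each vaccination, and Section 7.4 repeats bloods two days after vaccination.

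**The concern.** The primary objective compares the safety of the aerosol and intradermal routes. Of the two reactions that Section 4.4 pairs as most common, one is prompted and the other is not. A symptom that was never asked about cannot be recovered at analysis, so no later analysis document can repair this. The diary rule also speaks of Table 4 events and unexpected events; fatigue is expected but unlisted, and so fits neither term cleanly.

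The day 7 wording raises a different issue: which observations count as safety data. Group 2 receives intradermal MVA85A on day 0 and, before the amendment, aerosol MVA85A on day 28. Its day 7 bronchoscopy therefore follows an intradermal dose. If the day 7 sentences were taken to define the safety data, mucosal findings after the aerosol dose would sit outside that definition in the group whose regimen was changed because of respiratory events.

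**Working it through.** **1. Table 4 against the stated reaction profile.**

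| Symptom in Sections 2.1 and 4.4 | Row in Table 4? |
|---|---|
| Headache | Yes |
| Malaise | Yes |
| Feverishness | Yes |
| Muscle aches | Yes (myalgia) |
| Fatigue | No |

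Four of the five named symptoms are prompted. The one left out is one of the two called most common.

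**2. How many volunteers this concerns.** Inputs: 12 per arm and 36 in total (Section 9.1); 50-90% (Section 4.4).

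Expected cases = n × p.
- Per arm: 12 × 0.5 = 6; 12 × 0.9 = 10.8.
- Whole trial: 36 × 0.5 = 18; 36 × 0.9 = 32.4.

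This is one reading of the range. Section 4.4 attaches 50-90% to fatigue and headache, while Section 2.1 attaches it to the systemic symptoms together. Neither gives a rate for fatigue alone.

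**3. How much would be missed.** The documents give no capture fraction for unprompted reports. Assuming a fraction f between 0.25 and 0.75 only to show the dependence:

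Recorded cases per arm = 12 × p × f.
- Lowest: 12 × 0.5 × 0.25 = 1.5.
- Highest: 12 × 0.9 × 0.75 = 8.1.

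The range is too wide to serve as an estimate. Only the direction, downward, is secure.

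**4. Effect on the route comparison.** If f is the same in two arms with true rates p₁ and p₂, the recorded difference is f × (p₁ − p₂). A shared missing prompt does not create a difference between routes but shrinks a real one. If f differs by arm, the recorded difference is f₁p₁ − f₂p₂ and can mislead in either direction.

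**5. Day 7 wording against Table 1.** First the table's own blood volumes: 50 + 64 + 20 + 66 + 60 + 60 + 20 + 66 + 60 + 60 + 60 = 586 mL, and every cumulative entry agrees.
- Day 35: 60 (immunology) + 4 (biochemistry) + 2 (haematology) = 66 mL. The immunology row allows at most 60 mL, so the stated volume needs the 6 mL of safety blood.
- Day 30: 16 + 4 = 20 mL. The volume alone would also fit 20 mL of immunology, but Table 1 marks biochemistry on day 30 and the v1.3 entry in the amendment list gives the 16 and 4 mL split.

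Scheduled after day 7: 2 of 5 biochemistry draws, 1 of 3 haematology draws and 1 of 2 bronchoscopies. None of these appears in the two day 7 sentences; Section 4.5 also leaves out the day 2 biochemistry.

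**The case against.** **On fatigue.** The best reply is that nothing is lost. Section 8.3 records all adverse events, volunteers may report any new symptom, and unexpected events can simply mean those not on the list. Malaise, a neighbouring term, is prompted, and the reactions are described as nearly always mild. All arms use the same list and volunteers are blinded by paired placebo, so the missing prompt should act alike in each arm. The diary card itself is not in the document. Most of this stands: fatigue loses its prompt, not its place in the record, and no spurious route difference follows. It does not explain why headache is prompted and fatigue is not, and counting fatigue as malaise would merge two symptoms that the protocol lists apart.

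A reader might go further and say that the recorded rate is halved, or that results cannot be compared with earlier MVA85A trials. The first needs a capture fraction and the second needs the solicited lists of those trials; the protocol gives neither.

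**On day 7.** A reader might infer that safety capture stops at day 7, so that Group 2 has no blood or mucosal assessment after aerosol vaccine. The documents do not support that. Neither sentence says that day 7 is the only time point. The trial summary and Section 7.5 refer to Table 1 for timing, Section 4.1 expects safety information from the day 35 bronchoscopy in amended Group 2 volunteers, and Section 4.5 counts bronchoscopic examination as a safety source without naming a day. What remains is a contradiction in wording. The aerosol-exposure argument also does not reach Group 2 volunteers due their boost on or after 2 September 2015, who receive placebo by both routes on day 28.

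**Conclusion.** Two faults in the document hold.

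First, Table 4 omits a reaction that the protocol itself ranks among the two most common. Fatigue is collected only by unprompted report and is likely to be under-ascertained in the primary safety data. It could concern 6 to 10.8 of 12 volunteers per arm if the 50-90% range applies to fatigue itself; the number unrecorded cannot be computed. The direction rests on the assumption that unprompted reporting catches fewer cases than prompting, and that the diary card follows Table 4. A wider claim that the primary safety data as a whole are under-ascertained is not supported.

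Second, Sections 4.5 and 8.3 are narrower than Tables 1 and 3 and Sections 4.1 and 7.4. Post-boost procedures are scheduled, so the residual risk is that day 30 and day 35 bloods or day 35 mucosal appearance are not treated as safety data. This weighs most for Group 2 volunteers who received aerosol MVA85A on day 28. Both faults are cheap to correct and bear on the primary endpoint, so they should be corrected.

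**What to change.** **Fatigue.** Add a fatigue row to Table 4 and a matching line to the diary card. Flag each volunteer's fatigue data as prompted or unprompted, and report the two separately by arm. Make no pooled route comparison of fatigue if prompting differs between arms. This safeguard is needed because Section 4.3 describes a separate restart of Group 2 enrolment: if later volunteers fall mainly in that group, a new prompt would tie ascertainment to arm, a difference that the present list does not create. The cost is one diary line and one flag. The downside is that volunteers past their diary periods remain unprompted, so fatigue data will be of two kinds.

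**Day 7 wording.** Reconcile Sections 4.5 and 8.3 with Table 1 and Section 4.1, and state explicitly that post-boost bloods and mucosal appearance at the day 35 bronchoscopy belong to the safety data. This is a text correction and adds no visit, sample or procedure to those in Table 1.
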